Recent evidence has shown that overtreatment of musculoskeletal disorders does not lead to improved outcomes. Hopewell et al [17] found that a single session of education and self-management advice with a PT was noninferior to 6 sessions of in-person progressive exercise in improving pain and function among individuals with subacromial shoulder pain. Similarly, Katz et al [18] found that a self-directed home exercise plan alone was noninferior to 14 sessions of PT-guided exercise and manual therapy for pain reduction in individuals with meniscal tear–related knee pain. AT is lacking in trials to gauge the minimal effective dosage of exercise interventions. Pivoting to expand access through novel care delivery pathways is now more feasible, given the evidence that pain and function can improve with focused minimal care [19].

Clinicians currently lack evidence-based prognostic factors to differentiate patients who will benefit from rehabilitation from those who are less likely to respond [20,21]. Given that 26% to 47% of individuals with AT proceed to injections or surgery [22-24], the identification of prognostic factors could inform more efficient and personalized care. For nonresponders to rehabilitation, delays in progressing to invasive treatments prolong Achilles tendon pain, waste patient time and health care resources, and increase the total number of limited duty days as multiple treatments are tried. There is a critical need for a large, prospective study to identify factors that predict which patients with AT are most likely to respond to rehabilitation.

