### Secondary Outcomes

At baseline, we will capture demographics, military status, and tendon anterior-posterior diameter using ultrasound imaging [57]. In alignment with the core domain of tendon health, as defined by the International Scientific Tendinopathy Symposium Consensus [58], we will capture additional measures of pain and disability, along with measures of participation in life activities, physical function and capacity, psychological factors, patient rating of the condition, and quality of life over time (Table 3). Activity level will be captured using the Tegner scale [59], minutes per week spent doing moderate and vigorous physical activity, and questions about military readiness (eg, ability to complete a 2-mile run, wear military boots, and wear load-bearing equipment). Potential confounders that may influence the response to rehabilitation will also be captured, including the use of cointerventions or medications, self-reported exercise logs, and completion of educational units as captured in the learning management system. To assess treatment credibility, participants will complete a series of items evaluating the intervention’s impact on their perspective, understanding of self-management strategies, clarity of information, and appropriateness of the approach for managing AT, rated on a 5-point Likert scale (0=not at all, 1=a little bit, 2=somewhat, 3=quite a bit, and 4=very much).

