### Data Analysis

Baseline characteristics will be presented as counts and percentages for categorical measures. Continuous measures will be reported as means and SDs or medians and IQRs, as appropriate. Summary statistics by group will be provided for the primary and secondary outcomes and will be compared using 2-sample *t* tests, Wilcoxon rank-sum tests, or Fisher exact tests, as appropriate. Our intention-to-treat analysis will use linear mixed-effects models to assess the noninferiority of the single-visit intervention compared to the multivisit intervention, adjusting for baseline values of the primary outcomes. Additional intention-to-treat analyses will include any covariates that differed between groups at baseline. Primary outcomes will be the 4-week changes in measures of pain and function, and models will account for site using a random effect. Point estimates, CIs, and *P* values will be obtained for between-group differences in 4-week mean change compared to the margin of noninferiority. Significance for testing pain and function will be assessed at an *α* level of .025. We plan to report all data disaggregated by sex, AT type, and AT duration.

Secondary analyses will use linear mixed-effects models to examine predictors of improvement in pain and disability separately at 4 weeks. The same analysis will be performed at 12, 26, and 52 weeks as secondary end points. Outcomes will be the changes measured at each follow-up time point, and the models will be controlled for the corresponding baseline values. Model selection will be conducted to identify the optimal predictor set for each change outcome over time. The pool of candidate predictors includes baseline demographic and ultrasound imaging variables, as well as immediate improvement (within 2 weeks) of pain-related psychological factors, knowledge on self-management, pain, and disability. Models for all additional predictor combinations up to order 3 will be fit, and the Akaike information criterion will be calculated to compare model fits with the same outcome. Point estimates, CIs, and *P* values will be reported for predictors in models selected by the Akaike information criterion for each outcome. Significance for model predictors will be assessed at an *α* level of .05. Categorization of continuous variables using clinically meaningful cut points, such as obesity categories for the continuous BMI variable, will also be explored.

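### CIs and P values for prognostic factors are taken from the AIC-selected model on the same data, so the stated .05 level and the intervals do not hold for the predictors reported

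*Protocol article*

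**What the plan says.** The prognostic analysis serves the second of the two aims named at the end of the Introduction. That section also states a need to "identify factors that predict which patients with AT are most likely to respond to rehabilitation". The Data Analysis section fixes the procedure in four steps:

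- Purpose: "Model selection will be conducted to identify the optimal predictor set for each change outcome over time".
- Search: "Models for all additional predictor combinations up to order 3 will be fit, and the Akaike information criterion will be calculated".
- Reporting, for estimates, CIs and P values: "values will be reported for predictors in models selected by the Akaike information criterion for each outcome".
- Decision rule: "Significance for model predictors will be assessed at an *α* level of .05".

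The search is run separately for pain and disability at 4 weeks and again at 12, 26 and 52 weeks, with the baseline value of the outcome controlled for. The classes of candidate predictor are named, but their number is not given. The analyses are labelled secondary.

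**The concern.** A P value or CI from a regression model has its stated properties if the model was fixed before the data were seen. Here the model is the winner of a search, and the terms that win are partly those whose chance association with the outcome was largest. Ordinary standard errors ignore that, so intervals are too narrow for the predictors that get reported, and weak effects look larger than they are.

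This is a stated rule and not a detail left out. An analysis plan not shown could correct it only by changing the rule. What is at stake is the credibility of the second aim. The Introduction says that prognostic factors could inform care and links late recognition of nonresponders to delayed invasive treatment, so readers may take a reported factor and its interval at face value.

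**Working it through.** **Inputs.**
- From the article: 64 per group before dropout (Power Calculation), so n = 2 × 64 = 128; subsets of up to three predictors; alpha .05 for each predictor; baseline value forced in.
- Assumption: the pool size K. The baseline classes ("we will capture demographics, military status, and tendon anterior-posterior diameter using ultrasound imaging") suggest about 4–5 variables. The 2-week changes (psychological measures, knowledge, pain, disability) suggest about 6–7. That gives K of about 10–12; 3 to 20 was examined.
- Up to order 3 is read as subsets of one to three predictors. If it also means interactions, the search is larger.

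**Size of the search.** For K=12: C(12,1) + C(12,2) + C(12,3) = 12 + 66 + 220 = 298 models, plus the empty model.

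**The stated figure, checked by hand.** The only stated figure is the .05 level. AIC keeps one extra term when −2 log-likelihood improves by more than 2, and P(χ² on 1 df > 2) = .157. With a single noise candidate, the chance of P<.05 given that it was kept is .05/.157 = 32%, not 5%. Its 95% CI then covers zero in about 68% of cases. So the level is not reproduced even in the simplest case.

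**Simulation of the full search.** The outcome is pure noise. Intercept, baseline, arm and site are forced in (site as a fixed effect, a simplification of the planned random effect). All subsets of 0–3 candidates are fitted, the lowest AIC is kept, and ordinary P values and CIs are read from the winner. The table gives the chance of at least one P<.05 predictor per search.

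| K | 1 − .95^K (no selection) | AIC search, independent | AIC search, correlation 0.3 |
|---|---|---|---|
| 3 | 14% | about 15% | 16% |
| 5 | 23% | 24% | 27% |
| 8 | 34% | 35% | 42% |
| 10 | 40% | 44% | 50–53% |
| 12 | 46% | 50–51% | 57–60% |
| 20 | 64% | 70–72% | 81% |

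With n=160 the results agree within about 2 points.

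**Coverage of nominal 95% CIs for the selected predictors (K=12, n=128).**
- No real predictor: 52–63% across runs, the upper end for independent candidates. With only 6 candidates it is still 66%.
- Three weak true predictors (assumed partial R² about 3% each): 75–81%, with coefficients of selected true predictors inflated by roughly 25–45%.
- Three strong true predictors (assumed standardized effects 0.6, 0.5, 0.4): about 94–95%.

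**Controls.** One model with all 12 candidates restored coverage to about 95%. Selecting on one half of the data and testing on the other gave 4.6–5.3% rejection per selected noise predictor. The shortfall therefore comes from selecting and testing on the same data.

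**How much is selection, how much multiplicity.** In all-noise data with K=12, the full model without any selection still shows at least one P<.05 predictor in 41–47% of trials, against 50–60% for the AIC search. Selection adds only part of that rate. Its own damage is to the coverage and size of what is reported.

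**The case against.** Four points deserve weight.

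**The false-factor rate.** A reader might infer that AIC selection makes about half of all-noise searches produce a false factor, or multiply up to about 0.69 × 8 = 5.5 false factors over the eight searches. Neither is supported. Twelve unselected tests at .05 already give 46%, and a full model would give about 12 × .05 × 8 = 4.8 false factors on the same arithmetic. The count also assumes that nothing predicts anything, and it rests on a pool size that the article does not give. This objection stands in full.

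**The all-noise setting is unlikely.** The candidates include 2-week improvement in pain and disability, which may well predict 4-week change in the same measures. With three strong predictors the three slots are filled by real factors: coverage is about 95% and false factors appear in at most 2–4% of searches, against 36–38% for an unadjusted full model. This stands as a limit on the size. It does not rescue the rule, because the strong effects are assumed. With two strong predictors, coverage over all selected predictors is 82% and a false factor still appears in 37–42% of searches.

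**What the article leaves out.** It describes no internal validation, but a condensed article may leave that to the full plan, so no criticism is made of it. Searching anew at each time point is a legitimate choice, since different factors may matter later.

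**Status.** The analyses are secondary, and the noninferiority tests, their alpha and the sample size do not depend on them. This stands and limits the severity.

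**Conclusion.** The point holds for the inference attached to the selected predictors. As written, the .05 level and the 95% CIs are not valid for the factors that will be reported, whatever the pool size. How far off they are depends on the truth. Under the assumptions of 12 candidates and n=128, coverage is about 52–63% if no predictor is real, 75–81% with three weak ones, and near nominal with three strong ones.

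The chance of at least one false factor per all-noise search is about 44–60% for 10–12 candidates (about 15% for 3, 81% for 20 correlated candidates). It should be described mainly as uncorrected multiplicity across candidates. A reader might also infer that the trial's main result is compromised. It is not: the primary noninferiority analysis is unaffected. Severity: should fix.

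**What to change.** - Fix the candidate list in advance. For each outcome and time point, take estimates, CIs and P values from one model holding all of it. With 12 candidates this is 128/12, or about 10.7 participants per candidate. A selection-aware method, such as bootstrapping the whole search, is an alternative.
- Keep the AIC-selected set as a descriptive, parsimonious summary without significance claims.
- The full model alone does not deal with multiplicity, so control it across candidates (for 12, Bonferroni would be .05/12 = .0042). Alternatively, limit formal .05 tests to the predictors hypothesised in the Introduction: 2-week improvement in self-efficacy, pain and disability. Three such tests still carry 1 − .95³ = 14% if all are null and independent, which should be acknowledged.

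The cost is wording in the analysis plan and a little computing, with wider intervals and fewer factors called significant. Nothing in the conduct of the trial changes. With 15 participants enrolled as of January 2026, the change can be made before most outcome data exist.

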### Missing Data

Reasons for missing data will be recorded and compared qualitatively between participants who drop out and participants who complete the study. Participant characteristics collected prior to dropout will be compared to those of participants who complete the study. For the primary imputation strategy, if comparisons show that participant characteristics do not differ meaningfully between those with and without missing data, we will assume the data are missing at random and proceed accordingly. Under this assumption, we will use multiple imputation of the missing values for variables included in the linear mixed-effects models. Multiple imputation will be performed using SAS PROC MI and PROC MIANALYZE procedures in SAS software (version 9.4; SAS Institute Inc).

All variables in the primary analyses and, if feasible, other variables in the study database predictive of the missing values or influencing the cause of missing data will be included. For the sensitivity analyses addressing missing not at random, if assessment of reasons for missing data suggests that data may be systematically related to unobserved values (eg, inability to attend the next day assessment due to severe AT pain), sensitivity analysis will also be performed to assess the potential impact of including missing not at random data in the analysis. Methods for sensitivity analysis such as marginal delta adjustment, conditional delta adjustment, reference-based controlled imputation, and other pattern-mixture models will be considered. If needed, variables will be transformed to satisfy approximate normality before imputation and then retransformed to the original scale.

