### Power Calculation

The trial is powered to evaluate noninferiority between the two treatment groups at 4 weeks for 2 coprimary outcomes: (1) movement pain on a 0‐10 NRS, using a 1.1-point noninferiority margin, and (2) disability using the VISA-A, with an 8.2-point noninferiority margin. Both margins are consistent with previously published clinically meaningful thresholds [40]. Because the primary analysis will evaluate both outcomes using separate noninferiority tests, we applied a Bonferroni-adjusted, 2-sided *α*=.025 for each outcome. Power calculations assume comparison of mean group differences at 4 weeks using the same linear mixed-effects models planned for the primary analysis with adjustment for baseline values. A sample of 64 participants per group provides ≥80% power to conclude noninferiority for each outcome at *α*=.025. To account for an anticipated 20% dropout, we inflated the sample size to 80 participants per group.

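### Multiple imputation under MAR is made conditional on dropouts resembling completers, which is the wrong way round; no primary handling is stated for when they differ

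*Protocol article*

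**What the plan says.** All of the relevant text is in the Protocol article, mostly under Missing Data.

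- **Condition for MAR** (the quote stops one word short of the term): "if comparisons show that participant characteristics do not differ meaningfully between those with and without missing data, we will assume the data are missing at".
- **Consequence:** "Under this assumption, we will use multiple imputation of the missing values for variables included in the linear mixed-effects models". The section does not say what the primary handling is when the groups do differ.
- **Imputation model:** beyond the primary-analysis variables and if feasible, "other variables in the study database predictive of the missing values or influencing the cause of missing data will be included".
- **MNAR sensitivity analysis:** performed "if assessment of reasons for missing data suggests that data may be systematically related to unobserved values". The methods form an open list: "Methods for sensitivity analysis such as marginal delta adjustment, conditional delta adjustment, reference-based controlled imputation, and other pattern-mixture models will be considered". No reference arm and no direction for delta are given.
- **Primary model (Data Analysis):** a linear mixed model for 4-week change, adjusted for the baseline value, with site as a random effect, testing noninferiority of single-visit against multivisit.
- **Planned attrition (Power Calculation):** "To account for an anticipated 20% dropout", the sample is raised from 64 to 80 per group. No split by arm is given.

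**The concern.** The condition tests the wrong thing. If participants with and without missing data look alike, that is (weak) evidence for MCAR. MAR is the broader assumption that missingness may depend on what has been observed. A finding that dropouts differ on observed variables does not count against MAR; it is the situation in which imputing from those variables removes bias. Nor can any comparison of observed characteristics separate MAR from MNAR, so no result of the comparison justifies the rule. The criterion of a meaningful difference has no threshold, so the choice of primary method would rest on a judgement made after the data are seen.

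The rule also conflicts with its own section. Predictors of missingness are to enter the imputation model, yet finding such predictors defeats the stated condition for imputing.

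The direction of error matters in a noninferiority trial. The multivisit arm has 7 one-on-one telehealth visits and the single-visit arm is self-paced, so attrition that depends on early progress in one arm only is plausible. If single-visit participants who are doing poorly leave, an analysis of those who remain understates the deficit.

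**Working it through.** **1. The plan's own figure.** 64/(1 − 0.20) = 80 per group. This reproduces exactly, so the plan expects about 16 of 80 participants per arm to be missing.

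**2. Which mechanisms each analysis handles.** The Data Analysis model conditions on arm, baseline and site. On observed data it is unbiased if missingness depends only on those. It is not protected if missingness depends on the week-2 response, which the model does not contain. Imputation that includes week 2 is protected. Table 2 schedules survey measures at week 2, and Table 3 classes the VISA-A as a survey measure, so the data will exist. Movement pain is classed as performance-based and is not taken at week 2, so for that outcome the week-2 survey scores serve as auxiliaries only.

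**3. Size for the VISA-A.**

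Inputs:
- True deficit 8.2, the noninferiority margin (Power Calculation).
- SD 16.3, printed beside the MID in Table 3. It is not stated as the planning SD, so its use here is an assumption.
- 80 per arm.
- Assumed correlations: week 2 with week 4, 0.7; baseline with each, 0.5.
- Assumed dropout: random in the multivisit arm; in the single-visit arm rising as the week-2 score worsens, from weak to strong dependence (log-odds slope about 0.5 to 2 per SD).

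| Missing, single-visit / multivisit | Observed data, baseline-adjusted | Imputation with week 2 |
|---|---|---|
| 20% / 20% | about 7.5 to 6.1 | about 8.2 |
| 30% / 15% | about 7.2 to 5.3 | about 8.2 |

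The deficit is understated by (8.2 − 7.5)/8.2 = 9% to (8.2 − 6.1)/8.2 = 26% at the planned attrition. With 30% versus 15% it is understated by (8.2 − 7.2)/8.2 = 12% to (8.2 − 5.3)/8.2 = 35%.

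A hand check on plausibility: given baseline, the coefficient of week 2 for week 4 is (0.7 − 0.5 × 0.5)/(1 − 0.5²) = 0.6. A bias of 0.7 to 2.1 points therefore needs the retained single-visit participants to sit about 0.7/0.6 = 1.2 to 2.1/0.6 = 3.5 points above their arm's week-2 mean, after allowing for baseline. That is modest against an SD of 16.3.

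A milder scenario with no true difference and 19% versus 15% missing gave a bias of +0.06 SD in favour of single-visit, about 0.06 × 16.3 = 1.0 VISA-A point. Imputation with week 2 gave −0.003 SD (Monte Carlo SE about 0.003).

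**4. Reference-based imputation, if the multivisit arm were the reference.** With 20% missing, the expected difference is 0.8 × the true difference: 8.2 becomes 6.56 on the VISA-A, and 1.1 becomes 0.88 on the NRS. For the NRS:
- The SE implied by 80% power at one-sided .0125 is 1.1/(2.241 + 0.842) = 0.357.
- The estimate's sampling SD shrinks to about 0.8 × 0.357 = 0.286.
- Rubin's rules still report an SE near 0.355.
- False noninferiority at the margin is about Φ((0.22 − 2.241 × 0.355)/0.286) = Φ(−2.01) = 2.2%.

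Simulation with Rubin's rules gives 2.0% to 2.6% across variants, so about 2.5% against a nominal 1.25%.

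**The case against.** **The text does not forbid imputation when the groups differ.** A reader might infer that imputation is used only when dropouts resemble completers, and that an observed-data model is the declared fallback. The section is silent on that branch, and an article may leave it to a fuller document. This stands, so the biased estimates above are conditional on the natural reading. It does not rescue the stated condition, which is wrong in itself whatever a fuller document adds.

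**The plan already includes predictors of missingness.** That is sound MAR practice and covers part of the remedy. It also shows the inconsistency, because the practice presupposes the differences that the condition rules out.

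**Baseline adjustment may be enough.** If dropout depends only on baseline, arm and site, it is. The bias needs dependence on early response, which is plausible but assumed. The protocol gives one attrition figure and no split by arm, so the result is a range.

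**The sensitivity analysis could be read as favouring noninferiority.** The documents do not support that reading. Reference-based imputation is one of several options, no reference arm is named, and delta adjustment, which can be made conservative, is listed beside it. Choosing among the options is ordinary SAP content. It would mislead only if multivisit were the reference and single-visit truly worse, and then only in a sensitivity analysis. A calculation that treats the unshrunken SE as the sampling SD gives roughly double the error rate found above and should not be used.

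**A reader might also suppose that many significance tests would reject MAR by chance.** The plan specifies no such tests and no number of characteristics.

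**Conclusion.** The point holds for the MAR condition. The protocol ties MAR, and through it multiple imputation, to a pattern that bears on MCAR. It leaves the primary handling unstated where imputation is most needed, and it contradicts its own plan for the imputation model. If the observed-data model filled that gap, a VISA-A deficit at the margin would be understated by roughly 9% to 26% at the planned attrition and 12% to 35% with 30% versus 15% missing, in the direction of noninferiority. These sizes rest on the assumed SD, correlations and week-2-driven dropout in the single-visit arm; within the scenarios examined, the strength of dependence changes the size but not the direction.

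The conditional, open-ended sensitivity analysis is a secondary weakness. Recorded reasons are often unavailable for people lost to follow-up, so they are a poor trigger for it. This should be fixed, but it does not invalidate the design, because the harmful branch is inferred and the remedy is short.

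**What to change.** - Make multiple imputation under MAR the primary analysis whatever the dropout comparison shows. Put arm, site, the stratification factors, baseline values and the already scheduled week-2 survey scores in the imputation model.
- Keep the comparison of dropouts with completers as description only, with no role in choosing the method.
- Always run a delta-adjusted tipping-point analysis that penalises missing single-visit outcomes, rather than making it depend on recorded reasons.
- If reference-based imputation stays on the list, state that the multivisit arm will not be the reference for single-visit dropouts.

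The cost is a few sentences in the protocol or SAP and a little programming. No new data are needed and the sample size stays at 64 evaluable and 80 randomised per group. With 15 participants enrolled as of January 2026 and enrolment expected to run to 2028, the change can be made well before any comparative analysis.
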